## Abstract

**Introduction:**

The development of oral anticancer agents (OAA) has profoundly changed cancer care, leading patients to manage their chemotherapy treatment on an outpatient basis. The prevention of iatrogenic effects of OAA remains a major concern, especially since their side effects are not less serious than those of intravenous chemotherapy. The ONCORAL programme was set up to secure the management of OAA in cancer patients followed at the Lyon University Hospital. This multidisciplinary programme involves hospital pharmacists, nurses, oncologists, and haematologists, as well as community health professionals. Given the economic stakes that this programme entails for the health system, a medico-economic study was designed.

**Methods and analysis:**

This is a prospective controlled study, with individual open-label randomisation. A total of 216 outpatients treated with OAA and at risk of developing a drug-related iatrogenic event, will be randomised (2:1) to undergo follow-up in the ONCORAL programme or usual care. The primary outcome will be the estimation of the incremental cost-effectiveness ratio (difference in total costs per quality adjusted life years gained) at 12 months between the two groups. The secondary outcomes will be evaluation of OAA management consequences (relative-dose intensity, adherence, adverse drug events, drug–drug interactions, and proven medication errors), evaluation of overall survival and cancer-related quality of life, and patient-reported outcomes in relation to the treatment. A budget impact analysis will be implemented. Patient and health professional satisfaction regarding the ONCORAL programme will be measured.

**Ethics and dissemination:**

Approval to conduct this study was obtained from an Ethics Committee (*Comité de Protection des Personnes Ile-de-France VI*) in October 2019, and from the French data protection agency (*Commission Nationale de l’Informatique et des Libertés*), according to the French Law. Trial results will be disseminated at clinical conferences and published in peer-reviewed journals.

**Trial registration:**

NCT03660670.

STRENGTHS AND LIMITATIONS OF THIS STUDYThis study is the first cost-effectiveness evaluation of a multidisciplinary medication management programme for adult cancer outpatients treated with oral anticancer agents.A pragmatic open-label randomised design was adopted, based on a programme implemented in a French University Hospital, involving hospital health professionals (oncologists, haematologists, pharmacists, and nurses) and based on a structured relationship with the community health professionals who follow the patient.The cost-effectiveness will be estimated at 12 months, by comparing the difference in total costs and quality of life-adjusted years gained between the ONCORAL programme and usual care.Due to the nature of the interventions, patients and professionals participating in the study are not blinded to management allocation.

## Introduction

For many years, the treatment of cancer patients remained essentially hospital-based, relying on surgery, radiotherapy, and injectable chemotherapy. Since the early 2000s, oral anticancer agents (OAA), mostly targeted therapies such as tyrosine kinase inhibitors, have been steadily developed, contributing to significantly improve the prognosis of cancer patients.^1^

By allowing patients previously treated by injectable chemotherapy to receive oral therapy, the use of OAA has shifted patient management from hospital and healthcare provider administered treatment to self-administered treatment at home.^2^ Despite their high price, OAA were expected to reduce certain healthcare costs and were considered for their convenience and ease of administration.^3 4^

However, these drugs expose patients to iatrogenic risks, in part due to their narrow therapeutic index and complex pharmacological profile.^5^ They may also result in drug-related problems such as medication errors, adverse effects, and drug–drug interactions, which have been reported in half of the patients and considered as major in almost 20%.^6^ Importantly, OAA adherence may be reduced due to these drug-related problems and may be further complicated by the administration regimen, such as a discontinuous dosing regimen or combination with another OAA or injectable chemotherapy.^7 8^ In this context, the prevention of iatrogenic effects is crucial to enhance safety. Furthermore, as drug-related problems lead to an over-consumption of healthcare resources, this could lead to an increase in patient management-related costs.

It has been reported that patients show a preference for OAA over injectable chemotherapy, as the former meets their expectations in terms of comfort and autonomy.^9 10^ Their perception of efficacy and past treatments experience (including toxicity) may also influence this preference.^2^ It has been shown that for patients to successfully manage their OAA treatment, self-care support and multidisciplinary education across healthcare settings are needed.^11^ Finally, such medication management contributes to the optimal effectiveness of the treatment and a better quality of life.^12 13^

Structured OAA programmes have been set up in different countries and described in the literature, based on different components and organisation,^14^ highlighting the follow-up and monitoring of patients throughout their treatment.^15^ A promising effect has been described in the literature for certain adherence enhancing interventions, applied to target one or multiple factors influencing patient behaviour.^16^ The management of side effects should be more specifically included in OAA care programmes in order to help patients better identify them and improve their self-care behaviour.^11^ Although studies have also assessed the economic impact of pharmacist-led medication management programmes, showing cost savings and cost avoidance,^17 18^ none has evaluated the efficiency of such interventions on the whole patient pathway. There is thus still a need for rigorous studies to assess educational and counselling practices supporting adherence to OAA in terms of clinical benefit and efficiency.^19^

We set up a medico-economic study to evaluate, with a high level of evidence, the cost-effectiveness of a multidisciplinary OAA management programme for outpatients with cancer followed in a French University Hospital.

## Methods and analysis

### Study design and settings

A prospective controlled study with individual open-label randomisation was designed to compare two groups of outpatients treated with OAA at risk of developing a drug-related iatrogenic event and benefiting from follow-up consultations by an oncologist or haematologist from the Lyon Sud Hospital of the *Hospices Civils de Lyon*, France. Patients randomised to the intervention group will benefit from the ONCORAL programme, with enhanced multidisciplinary management involving hospital and community health professionals while patients randomised to the control group will be managed according to usual care.

Each eligible participant will be recruited following the consultation for an initiation or change of OAA with a hospital oncologist or haematologist. If the patient is ambulatory, deemed to be at important risk of developing drug-related iatrogenic events with OAA, and meets all the inclusion criteria (table 1), he will be informed orally and with a detailed written notice by the investigator. Randomisation will be set up after obtaining informed consent, in accordance with the principals of good clinical practice.

**Table 1 T1:** Patient eligibility criteria

Inclusion criteria	Exclusion criteria
Adult over 18 years of age	Treatment with OAA under a clinical trial or compassionate use
Diagnosed cancer	Treatment managed at home by a caregiver exclusively
Ambulatory status (not hospitalised for the management and treatment of the cancer)	No declared attending physician
Initiation or change of OAA (indication in the context of the marketing authorisation)	No or ≥2 declared regular community pharmacies
Sufficient autonomy to manage the treatment at home*	Participation in a clinical trial that may modify the costs of care
No major psychiatric cognitive disorder likely to interfere with the ONCORAL programme*	Legal protection or institutionalisation
Considered by the oncologist to be at risk of drug-related adverse events, or to have three or more of the following risk factors for developing a drug-related adverse event:	
≥2 OAA prescribed in combination	
≥2 lines of treatment	
Combination with an injectable chemotherapy protocol	
Discontinuous OAA regimen	
≥2 associated chronic conditions	
≥5 associated drugs including OAA	
Creatinine clearance<60 mL/min	
Frailties and psychosocial conditions (isolated patient, foreigner, and limited autonomy)	

*According to the treating oncologist.

OAA, oral anticancer agent.

The allocation of patients to the two study groups will be done via a centralised online randomisation system, in an unbalanced ratio 2:1 between the ONCORAL programme and usual care. Allocation will not be blinded to participants, medical staff, nor the clinical trial staff.

During the course of the study, in the event of a change in treatment and/or complete discontinuation of OAA, the patient will be withdrawn from the study; however, its data will be considered and analysed.

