#### The ONCORAL programme

The ONCORAL multidisciplinary programme has been described elsewhere.^20 21^ Monthly interviews are carried out with a hospital pharmacist and/or a nurse after each consultation with the oncologist or haematologist in the hospital or by telephone if no consultation is scheduled. It is carried out for the entire duration of the OAA treatment and will be assessed in the context of the study up to 12 months after beginning of treatment (ie, patient’s inclusion).

Briefly, the therapeutic education sessions are personalised, taking into account the specific needs of each patient. They cover issues relating to understanding the medication plan, including all drugs prescribed to the patient, and the management of side effects and the prevention of drug–drug interaction, including self-medication. If the pharmacist detects an interaction, the prescribing physician is contacted to manage it jointly.

All the community health professionals involved in the patient’s care (ie, the attending general practitioner, the community pharmacist, and the home nurse, if any) are informed of the patient’s participation in the ONCORAL programme and of all relevant information gathered during the sessions, and are encouraged to share all advice given to the patient using an individual liaison booklet.

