Studies reporting pharmacist-led collaborative medication management programmes for OAA have described outcomes to support their benefit, such as patient safety in terms of iatrogenic events, notably drug-related problems that can be identified and solved, and improvement in adherence.^17 33–35^ The present study will assess consequences of OAA management in terms of clinical outcomes: the RDI reflects the changes in prescription that are made as a result of chemotherapy-induced iatrogenic events, and which therefore have an impact on therapeutic effectiveness.^36^ The ONCORAL programme should ensure a higher RDI compared with usual care by maintaining adherence to the treatment, notably by educating patients on how to anticipate and manage adverse events. QALYs, which are the remaining years of life for patients and are weighted by a quality of life score, are a particularly important outcome when dealing with cancer patients. QALYs will be used to estimate the cost-effectiveness ratio of the ONCORAL programme compared with usual care, in accordance with the methodological standards of medico-economic studies.^37^ To complete the cost analysis of the ONCORAL programme, a microcosting study will be carried out from the hospital perspective, since it is the hospital that is currently financing the additional human resources required for this intervention. This analysis will provide additional and relevant information for hospital decision-makers in order to maintain funding, but also for the French insurance system if payment of a dedicated sum could be considered to extend this intervention to the national level.

Another strength of the study is its pragmatic approach, as the ONCORAL programme is already implemented in the participating centre. There will be no additional intervention for the control group that could impact usual care; patients will only be asked to complete the booklet and questionnaires. Despite the deployment of the ONCORAL programme, not all eligible patients can benefit from it today on a routine basis for financial and logistical reasons. A 2:1 ratio was adopted to randomise patients, as this approximates the number of patients currently being monitored by ONCORAL in current practice.

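### Patients changing OAA can be enrolled after earlier ONCORAL follow-up at the same centre, so some controls may already be trained; the protocol's contamination argument does not cover this route

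*Protocol article*

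**What the plan says.** **Eligibility.** Under Study design and settings, patients are "recruited following the consultation for an initiation or change of OAA with a hospital oncologist or haematologist", and Table 1 repeats this as "Initiation or change of OAA (indication in the context of the marketing authorisation"). The table prints six exclusions: OAA given in a trial or as compassionate use, treatment handled only by a caregiver, no attending physician, no single regular pharmacy, another trial that affects costs, and legal protection or institutionalisation. Past or current ONCORAL follow-up is not among them. The randomisation paragraph describes a central 2:1 allocation and does not mention prior exposure.

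**Existing use of the programme.** The Discussion states that "the ONCORAL programme is already implemented in the participating centre" and that "A 2:1 ratio was adopted to randomise patients, as this approximates the number of patients currently being monitored by ONCORAL in current practice". It adds that "not all eligible patients can benefit from it today on a routine basis for financial and logistical reasons". The section on the ONCORAL programme says of the follow-up: "It is carried out for the entire duration of the OAA treatment".

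**Contamination.** In its paragraph on limitations, the Discussion concludes that the groups cannot contaminate each other. It gives two reasons: two patients rarely share a community pharmacy, and controls are not followed at the hospital pharmacy.

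**The concern.** Routine ONCORAL follow-up lasts as long as the OAA does, and the trial recruits when an OAA is started or changed. A patient who has been in routine ONCORAL and now changes drug is therefore eligible by the printed criteria at that moment. If allocated to usual care, this patient contributes a contrast between stopping and continuing the programme, whereas the objective is ONCORAL against usual care.

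The programme teaches skills that could outlast one drug: managing side effects, avoiding interactions including those from self-medication, and understanding the whole medication plan. The Discussion itself expects RDI to rise through education on anticipating and managing adverse events. If controls keep part of that benefit, the differences in RDI, adherence and QALYs shrink, while the staff time of new sessions is still costed to the ONCORAL arm. A small or null difference could then be misread as a programme that does little.

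Both reasons given against contamination concern what happens after allocation. Neither bears on sessions received before it.

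**Working it through.** **1. The plan's own figure.** Inputs from Sample size calculation: RDI 0.70 against 0.85 (difference 0.15), SD 0.35, two-sided 0.05, power 80%, ratio 2:1.

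Controls needed = (1 + 1/2) × 0.35² × (1.960 + 0.842)² / 0.15² = 64.1, rounded up to 65, with 130 in the ONCORAL group. This matches the plan.

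Standard error = 0.35 × √(1/65 + 1/130) = 0.0532. Then 0.15 / 0.0532 = 2.82, and power is 80.5%.

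**2. Attenuation model.** Let

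- f = share of recruits who change from an earlier OAA given at the centre (not in the document);
- 2/3 = share of those changers previously in ONCORAL (a reading of the 2:1 statement; no percentage is printed);
- c = fraction of the programme's effect that a previously followed control retains (not in the document).

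The ONCORAL arm mean and the SD are held fixed. The expected RDI difference is

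0.15 × (1 − f × 2/3 × c).

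**3. Results with 130 + 65 evaluable patients.**

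| f | c | previously followed controls, f × 2/3 | factor | RDI difference | power |
|---|---|---|---|---|---|
| 0 | – | 0% | 1 | 0.15 | 80.5% |
| 0.1 | 0.25 | 6.7% | 0.983 | 0.1475 | 79% |
| 0.25 | 0.5 | 16.7% | 0.917 | 0.1375 | 73% |
| 0.3 | 0.5 | 20% | 0.90 | 0.135 | 72% |
| 0.5 | 0.5 | 33.3% | 0.833 | 0.125 | 65% |
| 0.5 | 1 | 33.3% | 0.667 | 0.10 | 47% |
| 0.6 | 1 | 40% | 0.60 | 0.09 | 39% |

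With 72 controls enrolled, f = 0.25 to 0.5 means about 12 to 24 previously followed controls (72 × 0.167 and 72 × 0.333).

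**4. The ICER.** The document gives no cost or QALY assumptions, so no absolute figure can be derived. If the QALY gain shrinks by the same factor and the cost difference stays the same, the ratio is multiplied by 1/0.983 = 1.02, 1/0.90 = 1.11 or 1/0.60 = 1.67 in the three scenarios f = 0.1, 0.3 and 0.6. The cost difference would probably move too, because avoided costs would also be attenuated while programme costs would not. These multipliers are illustrations only.

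**The case against.** The strongest reply is that nothing shows this happened. The document does not say that a patient already in ONCORAL was approached or randomised, and it gives no count. The two-thirds is an inference from a sentence without a denominator, and the Discussion stresses that coverage is partial. This stands: entry of trained controls is permitted by the criteria and plausible, but not documented.

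A reader might also infer that listing "≥2 lines of treatment" as a risk factor selects patients with earlier ONCORAL exposure. It need not. It is one of eight factors, of which three are required unless the oncologist judges the patient to be at risk, and an earlier line may have been injectable.

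Carry-over has no source in the document either. Much of the programme is continuing work on the current regimen, which a control loses, and RDI is defined for the OAA being taken. Full retention is therefore an extreme case, and the range has to start near zero.

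A reader might further infer that the ICER becomes invalid. It does not. Randomisation balances prior exposure in expectation, so the comparison remains internally valid for patients starting or changing OAA at this centre. The consequence is attenuation relative to a population new to the programme.

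Finally, a reader might infer that a patient withdrawn at an OAA change could be randomised again. No passage provides for a second entry, participants carry a unique identification number, and rules on repeat enrolment are normally left to the full protocol, which is not shown. That inference is not supported.

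What the reply does not remove is that the printed eligibility table leaves this route open and that the categorical contamination statement does not address it.

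**Conclusion.** The point holds as a possible attenuation of unknown size. By the printed criteria, controls may have had ONCORAL education before randomisation, and the reasons given for excluding contamination do not reach that exposure. The bias would be towards a smaller difference in RDI, adherence and QALYs.

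The size runs from negligible (RDI difference 0.1475, a loss of 1.7%) to large (0.09, a loss of 40%). It rests on three quantities that the document does not fix: the share of changers, the share of them previously in ONCORAL, and the retained effect. The sample size calculation itself is correct for the contrast that it assumes. The first two quantities can be established from existing records, so the question need not stay open.

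**What to change.** - Keep the full intention-to-treat comparison as primary.
- Before database freeze, take prior ONCORAL follow-up (yes/no) for every randomised patient from the programme's own records, and report it by arm.
- In the statistical analysis plan, which the article says will precede the freeze, prespecify a supporting ICER and RDI comparison restricted to ONCORAL-naive patients.
- Qualify the contamination statement in the Discussion: its reasons cover exposure during the trial, and exposure before randomisation is examined separately.

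Eligibility need not change. With 191 randomised of the 215 planned under Sample size calculation, new exclusions would affect only about 24 patients (215 − 191) and would make the cohort less uniform.

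The cost is one variable and one supporting analysis that is less precise than the primary. With f = 0.3, for example, 20% of patients drop out of the naive set, leaving 104 + 52 of 130 + 65. The standard error is then 0.35 × √(1/52 + 1/104) = 0.0594, and power for the full 0.15 is about 71%, close to the 72% of the attenuated full analysis in that scenario. The naive analysis therefore does not recover power. Its purpose is to show whether a small overall difference reflects earlier exposure. If prior exposure proves rare, the same data substantiate the contamination statement.

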#### Primary outcome

The primary outcome will be the estimation of the incremental cost-effectiveness ratio (ICER) at 12 months between the ONCORAL programme and usual care.

The impact of OAA management monitoring will be measured using QALYs that takes into account both survival and quality of life, which is particularly relevant in cancer. The number of QALYs will be assessed using survival time and the 3-level version of the EuroQol 5 Dimensions questionnaire (EQ-5D-3L).^22^

Cost calculations will include hospital-related and ambulatory costs over the 12-month period of the study, from a French health insurance perspective and a hospital perspective.

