#### Main analyses

The ICER will be expressed as the extra cost in euros per QALY gained following the introduction of the ONCORAL programme compared with the control group:^29^

$$ICER=\frac{C_{Oncoral}-C_{Control}}{QALY_{Oncoral}-QALY_{Control}}$$

where 
$C_{Oncoral}$
 and 
$C_{Control}$
 are the mean cost per patient in each group, and 
${QALY}_{Oncoral}$
 and 
${QALY}_{Control}$
 the mean number of QALY in each group.

The principle of calculating QALYs is to weight the time spent in health states by the preference scores associated with these states. Multiattribute health state classification systems are one of the methods of valuing health states. The EQ-5D-3L self-administered questionnaire is a multiattribute health state classification system whose preference scores are validated in France.^30^ Once the health states are described by the EQ-5D-3L, each of them is individually associated with the corresponding preference score.

A univariate sensitivity analysis will be performed to test the robustness of the cost-effectiveness analysis results and to identify the most sensitive parameters, using a Tornado diagram. The bootstrap method will be used to analyse the sampling uncertainty: 95% CIs of the parameters will be computed; and the joint uncertainty of costs and QALYs will be analysed using cost-effectiveness acceptability curves, which will represent the probability that the ONCORAL programme will be cost-effective at different willingness-to-pay thresholds.

Concerning the primary outcome, a complete case analysis, based on patients for whom all cost and effectiveness data are available, will be performed; an intention-to-treat analysis will be performed in the whole population after imputation of missing data.

Data regarding secondary outcomes will be described for each group. Missing data will be documented but there will be no imputation for secondary outcomes. A Kaplan-Meier model will be used to estimate the overall and the progression-free survival rates up to 12 months in each group, and a log-rank test will be implemented to compare them. Mixed models for repeated measures will be used to estimate the evolution of the different PROs and of cancer-related quality of life.

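### Withdrawing patients from the study when the OAA is changed or stopped leaves the 12-month QALYs, and so the primary ICER, without planned EQ-5D data after an outcome-related event

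*Protocol article*

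**What the plan says.** Study design and settings sets the rule: "in the event of a change in treatment and/or complete discontinuation of OAA, the patient will be withdrawn from the study". The sentence goes on: "however, its data will be considered and analysed". The withdrawal is from the study, not only from the ONCORAL sessions. The second clause retains data and does not say whether more are collected.

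The outcomes have a fixed horizon. Under Primary outcome: "The primary outcome will be the estimation of the incremental cost-effectiveness ratio (ICER) at 12 months between the ONCORAL programme and usual care". QALYs combine survival time with EQ-5D-3L utilities. For costs: "Cost calculations will include hospital-related and ambulatory costs over the 12-month period of the study". Under Data collection, patients complete the EQ-5D-3L themselves at inclusion and at the later study visits. Hospitalisation and ambulatory data are completed from the hospital information system and from ERASME.

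Main analyses plans two analyses of the primary outcome: "a complete case analysis, based on patients for whom all cost and effectiveness data are available, will be performed", and "an intention-to-treat analysis will be performed in the whole population after imputation of missing data". For survival, "A Kaplan-Meier model will be used to estimate the overall and the progression-free survival rates up to 12 months in each group". Secondary outcomes are not imputed.

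**The concern.** A 12-month comparison of all randomised patients needs 12 months of outcome for each of them, whatever happens to the treatment. The rule makes a post-randomisation treatment event the end of study participation. Patients commonly change or stop an OAA because of toxicity or progression, and both bear on utility, cost and death. The Discussion expects ONCORAL to raise relative dose intensity by helping patients stay on treatment and manage adverse events. The triggering event therefore lies on the programme's own pathway and may occur at different rates in the two arms.

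The denominator of the ICER is at stake. If EQ-5D stops at withdrawal, the estimated QALY difference depends on how unobserved time is filled in, and that time is not a random part of follow-up.

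**Working it through.** **1. The rule against what the outcomes need after withdrawal**

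- EQ-5D: tied to study visits. Nothing provides for completion by a patient who has left the study, so the loss follows from the text.
- Costs: partly drawn from the hospital information system and ERASME, which do not depend on study visits. Later costs could be recovered, but the article does not commit to this.
- Vital status: needed for QALYs and overall survival. It may be recoverable, but no source or commitment is stated for withdrawn patients.

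**2. The plan's own figure and its allowance**

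Inputs (Sample size calculation): RDI 0.70 against 0.85, SD 0.35, two-sided 0.05, power 80%, ratio 2:1.

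Control n = (1 + 1/2) × (1.960 + 0.842)² × 0.35² / 0.15² = 1.5 × 7.85 × 5.444 = 64.1, so 65, with 130 in ONCORAL and 195 in all. This reproduces the plan. The increase to 215 matches 195 × 1.10 = 214.5 and leaves room for 20/215 = 9.3% early withdrawal. The figure was set for RDI, not for the ICER, but it is the only withdrawal allowance in the article.

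**3. Hypothetical loss of data**

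The document gives no rate of OAA change or discontinuation. Assume a share p withdrawn by month 12 at a constant hazard, no further EQ-5D, and no other loss or death. Then λ = −ln(1 − p), and the observed fraction of the 12 months is p/λ.

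| p (assumed) | Full 12-month data, 215 × (1 − p) | Person-time unobserved, 1 − p/λ |
|---|---|---|
| 20% | 172 | 10% |
| 40% | 129 | 22% |
| 60% | 86 | 35% |

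**4. Hypothetical effect on the QALY difference**

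Assume 40% withdrawn in control and 30% in ONCORAL, with no deaths. Observed fractions: 0.40/0.5108 = 0.783 and 0.30/0.3567 = 0.841, a difference of 0.058.

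- Utility 0.70 throughout in both arms, so no true difference. Counting QALYs only to withdrawal gives 0.70 × 0.058 = 0.041 in favour of ONCORAL. At 50% against 35%, the fractions are 0.721 and 0.812 and the spurious gain is 0.064. With equal rates it is 0.
- Utility 0.70 on the OAA and 0.60 afterwards. The true gain is (0.70 − 0.60) × 0.058 = 0.006. Imputing 0.70 for the unobserved time gives 0.000. That zero is built in by assuming the same on-OAA utility in both arms.

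One handling overstates the gain and the other removes it, so the direction of bias depends on a choice that the collected data could not inform.

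**5. Hypothetical effect on overall survival, only if it were censored at withdrawal**

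Assume monthly hazards of 5% for stopping or changing the OAA, 1% for death on it and 6% for death afterwards.

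- True 12-month survival = e^(−0.06×12) + 0.05 × 12 × e^(−0.06×12) = 0.487 + 0.292 = 0.78.
- Kaplan-Meier with censoring at withdrawal estimates e^(−0.01×12) = 0.89.

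**The case against.** The strongest reply is that the article is a condensed account. The full protocol, the supplementary visit table and the SAP are not shown, and any of them may provide for follow-up after withdrawal. Retaining the data could also be read to include later data. This limits certainty, but the point is not a missing detail: the article states a rule, and read plainly the rule ends participation. A SAP cannot restore questionnaires that were never given.

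Several stronger readings are tempting and are not supported:

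- That costs are cut off at withdrawal. The routine sources could cover the full 12 months, so this is possible but not established.
- That overall survival is censored at treatment change. No censoring rule is given, so step 5 is conditional on one.
- That imputation must borrow from patients still on their first OAA. No imputation model is stated. What stands is that, without post-withdrawal EQ-5D, the assumption of any model about that period cannot be checked against trial data.
- That a dose reduction counts as a change in treatment. Usual care treats it as an ordinary prescription change, RDI as an outcome describes dosage changes, and the eligibility criteria refer to a change of OAA. Withdrawal at the first dose change would defeat the RDI outcome.

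It is also fair to say that every rate and utility in steps 3 to 5 is assumed and that no cost was modelled, so no bias in the ICER itself has been shown.

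**Conclusion.** The concern holds for EQ-5D and QALYs. As written, the rule ends study participation at an event related to outcome and possibly to allocation, while the primary outcome needs visit-based EQ-5D to month 12. Complete cases would be chosen mainly by whether patients stayed on their first OAA. The intention-to-treat analysis would cover everyone, but only through an untestable assumption about the unobserved period. For costs and vital status the loss is a risk that the text leaves open, and if overall survival were censored at withdrawal, that censoring would be informative.

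The size and direction of bias cannot be derived from the document. The illustrations show only that the effect need not be small: spurious QALY gains of 0.041 to 0.064 in some assumed cases, and loss of a true gain of 0.006 in another. The conclusion rests on reading withdrawal from the study in its ordinary sense and on no unseen document providing for continued collection.

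**What to change.** Amend the withdrawal rule so that change or discontinuation of the OAA does not end study follow-up. This concerns data collection only and takes no position on treatment. For every randomised patient, unless consent is withdrawn:

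- continue EQ-5D-3L at the scheduled visits to month 12;
- collect vital status to month 12;
- collect hospital and ERASME costs to month 12.

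For patients already withdrawn, recover vital status and costs retrospectively where consent allows. Make the intention-to-treat analysis using these data the main analysis, and the complete-case analysis a sensitivity analysis.

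The cost is an amendment and some extra questionnaires; the cost sources are already planned. The main limit is timing. The article reports 191 patients already randomised and completion expected by December 2024. EQ-5D already missed among them cannot be recovered, so the report should give the number withdrawn under this rule by arm, with timing and reason. If follow-up has closed, only the retrospective recovery and the choice of main analysis remain available.
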